### Analysis

The primary focus of this pilot trial is feasibility. Descriptive analyses will be undertaken to profile baseline characteristics of both the intervention and control groups, and to assess key feasibility outcomes. These include rates of recruitment, consent, retention, and adherence, as well as indicators of intervention acceptability and engagement at both the cluster and individual levels. These feasibility outcomes will be reported with corresponding proportions, means, and 95% confidence intervals, where appropriate. Pre-specified progression criteria (see above) will be applied to determine the feasibility of proceeding to a definitive trial.

The unit of analysis will be the individual adolescent, although randomization occurs at the school level. Clustering by school and class will be accounted for in multilevel models. Exploratory analyses of potential intervention effects will also be conducted. For binary outcomes, binomial distributions will be used, while normal distributions will be applied for continuous variables. Assumptions of normality, homogeneity of variance, and linearity will be examined; if violated, appropriate transformations (e.g., logarithmic or square root) will be applied. For missing data exceeding 5%, patterns and mechanisms of missingness will be explored, with multiple imputation used as appropriate. Sensitivity analyses will be undertaken to examine the impact of missing data and outliers.

To evaluate the potential efficacy of the intervention in reducing intention to use tobacco, a mixed-effects model will be employed. These models will control for baseline covariates at the individual, class, and school levels, incorporate minimization factors, and adjust for clustering by school. Given the small number of clusters (eight schools), small-sample corrections will be applied to reduce the risk of biased inferences. For continuous outcomes, the Kenward–Roger approximation (REML estimation) will be used to adjust standard errors and denominator degrees of freedom; if convergence issues arise, the Satterthwaite approximation will be applied. For binary or other non-Gaussian outcomes, simple cluster-level analyses will be conducted (e.g., calculating school-level outcome proportions and comparing these between groups using t-tests or non-parametric tests). All results will be interpreted with caution in light of the limited number of clusters, focusing on the direction and magnitude of the effect rather than on p-values, or highlighting the uncertainty in the estimates. Analyses will follow an intention-to-treat principle, supplemented by sensitivity analyses using multiple imputation.

Secondary exploratory analyses will adopt a repeated-measures approach to assess changes in tobacco knowledge, attitudes, beliefs, resistance skills, and mental well-being. Subgroup analyses will also be conducted (e.g., school year group = year 8 vs year 9, sex = male *vs* female, housing = living with parents vs without parents, family socioeconomic status = low-income *vs* middle/high-income, family/friends’ tobacco use = yes vs no, mental health condition = good vs poor, etc.) to provide preliminary estimates of potential differential effects. These analyses are exploratory, intended to generate hypotheses and to inform the design of a future definitive trial. Findings will be interpreted with extreme caution and will not be considered confirmatory.

All analyses will be conducted using Stata version 18.0, with the level of significance set at *p* < 0.05 for exploratory outcomes.

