**Methods:**

This pilot school-based cluster randomised controlled trial will be conducted among adolescents (*N *≈ 1280 participants) in school years 8 and 9 attending participating schools (*K* = 8 schools) in Dhaka, Bangladesh. The intervention consists of three 40-min sessions delivered over three successive days, incorporating knowledge- and skill-based lectures, interactive activities, and materials targeting tobacco prevention and health promotion. The intervention was developed based on evidence from a systematic review, a quantitative survey, qualitative focus groups, and expert consensus. The primary outcome is intervention feasibility, assessed through recruitment and attrition rates, fidelity of delivery, and acceptability. Secondary outcomes include changes in tobacco use intentions, tobacco-related knowledge, attitudes and beliefs, skills development, and measures of health and well-being. Data will be collected through structured questionnaires at baseline and at 1-month follow-up. A post-intervention process evaluation will be conducted with a sub-sample of pupils in the intervention arm and their teachers, using a mixed-methods approach to explore implementation processes, facilitation, participant experiences, and areas for improvement.

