## Methods

### Trial design

This study employs a pilot cluster randomised controlled trial (C-RCT) design. The unit of randomization will be schools, with the ultimate aim of informing a full-scale C-RCT. In addition, a mixed-methods approach will be employed for the process evaluation.

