#### Randomization

Given the risk of contamination within schools, individual randomization is impractical. Schools will instead be randomised into intervention or control arms using a cluster design. Stratification and matching will account for school location (based on local government boundaries), monthly tuition fees, and school passing rates to ensure balanced allocation. A random sequence generation method involving three stratified blocks (based on sex composition of the schools: girls only, boys only, and mixed sex) will allocate schools (four in each group) using computer-generated random numbers. Randomization will be concealed until allocation to minimise selection bias. While blinding of participants and researchers is not possible, independent data collectors will collect outcome data to minimise assessment bias. All data will be promptly entered into the UCL Data Safe Haven using REDCap software [39, 40]. The randomization process will be closely monitored, with any deviations from the protocol transparently documented in the final trial report. Figure 1 presents the recruitment and allocation process, while Table 2 outlines the enrolment, interventions, and assessment schedule in the SPIRIT flow diagram.

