### Sample size calculations

Formal sample size calculations are not typically required for pilot or feasibility studies [56]. The sample size for this trial was therefore guided primarily by feasibility considerations, particularly the need to estimate key parameters such as recruitment and retention rates, adherence to the intervention, and completeness of outcome data with acceptable precision. For example, with an overall sample of approximately 1280 participants (640 in each group), a retention rate of 85% could be estimated with a 95% confidence interval of ± 2.0%, providing a sufficiently precise estimate to inform planning for a future definitive trial [57, 58].

In addition to feasibility considerations, an exploratory calculation was conducted to provide a pragmatic estimate for recruitment targets and to assess the potential scale of a future definitive trial. This calculation, based on a potential efficacy outcome (intention to initiate tobacco use), is not intended to serve as the primary justification for the sample size. Instead, it offers supportive information by (i) demonstrating the plausibility of detecting an effect of interest, (ii) informing logistical planning and resource allocation, and (iii) providing preliminary data to estimate the variability of outcomes for a full-scale trial. For completeness, the details of this calculation are reported in Additional file 2.

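### The repeated-measures analysis of knowledge, attitudes, beliefs, skills and well-being names no school-by-time variation; with time-constant school and class intercepts only, the test of the intervention would be too liberal

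*Protocol article*

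**What the plan says.** Under Trial design, "The unit of randomization will be schools". Under Randomization, a stratified sequence "will allocate schools (four in each group) using computer-generated random numbers", so there are eight randomised units. The abstract gives two questionnaire times for the secondary outcomes: "Data will be collected through structured questionnaires at baseline and at 1-month follow-up".

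The Analysis section takes the individual adolescent as the unit of analysis and adds a general rule: "Clustering by school and class will be accounted for in multilevel models". For intention to use tobacco it describes a mixed-effects model with baseline covariates and adjustment for school. Because there are only eight schools, it adds Kenward–Roger for continuous outcomes, with Satterthwaite as the fallback. For the other named outcomes it says: "Secondary exploratory analyses will adopt a repeated-measures approach to assess changes in tobacco knowledge, attitudes, beliefs, resistance skills, and mental well-being". No arm-by-time estimand, random-effects structure, or school-by-time or class-by-time term is given for these.

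The section calls these analyses exploratory and not confirmatory, intends them to inform a definitive trial, and closes "with the level of significance set at *p* < 0.05 for exploratory outcomes".

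**The concern.** When an outcome is measured twice in each pupil and the model concerns change, the intervention effect is the arm-by-time term. A school intercept that is the same at both times shifts a school's baseline and follow-up scores equally, so it drops out of the change. A constant class intercept drops out in the same way. What remains at school level is the extent to which schools move differently over the month. If the model has no term for that, the arm-by-time contrast is compared with variation between pupils, although only eight schools were randomised.

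The stated safeguards do not catch this. Kenward–Roger adjusts standard errors and degrees of freedom for the variance components in the model. In an intercept-only model it finds no school-level component bearing on this contrast and returns pupil-level degrees of freedom. An analyst could therefore follow the wording exactly, report that clustering and small-sample corrections were applied, and still produce intervals that are too narrow. The planners of the definitive trial would also get no estimate of how much schools differ in change.

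**Working it through.** **The plan's own figure.** The article gives no error rate for these analyses. Its one computable precision figure is under Sample size calculations: "a retention rate of 85% could be estimated with a 95% confidence interval of ± 2.0" percentage points. The simple binomial formula reproduces it: 1.96 × √(0.85 × 0.15 / 1280) = 0.0196. This confirms the inputs only.

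**Inputs from the article.**
- Eight schools, four per arm (Randomization).
- Pupils: "with an overall sample of approximately 1280 participants (640 in each group"), so 1280 / 8 = 160 per school. At 85% retention, 0.85 × 160 = 136 have both measurements.
- Two measurement times; significance level 0.05, taken as two-sided because the side is not stated.

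**Assumptions, because the article gives no values.** Total variance 1 at each time; school ICC ρ = 0.01 to 0.10; correlation of the school effects across the two times c = 0.8 to 0.95; pupil autocorrelation 0.5. No separate class component is added.

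**Step 1: does the intercept cancel?** Three data sets (8 schools of 60 pupils, with schools differing in change) were fitted with school and pupil random intercepts plus arm, time and arm-by-time. The arm-by-time standard errors were 0.07569, 0.08294 and 0.07788. Ordinary least squares on pupil change scores gave the same estimates and the same standard errors to about four digits. Comparing school mean changes gave 0.217, 0.174 and 0.131. The intercept-only model thus behaves as an unclustered test of pupil change, with 8 × 136 − 2 = 1086 to 8 × 160 − 2 = 1278 degrees of freedom. For a class intercept the cancellation follows by the same algebra; it was not fitted.

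**Step 2: ICC of the change score.** The between-school variance of change is 2ρ(1 − c). The pupil-level variance is 2(1 − ρ)(1 − 0.5) = 1 − ρ. So r = 2ρ(1 − c) / [2ρ(1 − c) + (1 − ρ)]. Example: ρ = 0.05, c = 0.8 gives 0.02 / (0.02 + 0.95) = 0.0206.

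**Step 3: false-positive rate.** The true variance of the contrast is 1 + (m − 1)r times the modelled one, so the rate is 2[1 − Φ(1.96 / √(1 + (m − 1)r))]. In the example with m = 160: 1 + 159 × 0.0206 = 4.28, √4.28 = 2.07, and the rate is 34%.

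| School ICC | c | r | Rate, m = 136 | Rate, m = 160 |
|---|---|---|---|---|
| 0.01 | 0.95 | 0.0010 | 6.6% | 6.9% |
| 0.01 | 0.8 | 0.0040 | 11% | 13% |
| 0.02 | 0.95 | 0.0020 | 8.3% | 8.8% |
| 0.02 | 0.8 | 0.0081 | 18% | 19% |
| 0.05 | 0.95 | 0.0052 | 13% | 15% |
| 0.05 | 0.9 | 0.0104 | 21% | 23% |
| 0.05 | 0.8 | 0.0206 | 31% | 34% |
| 0.10 | 0.95 | 0.0110 | 21% | 24% |
| 0.10 | 0.8 | 0.0426 | 45% | 48% |

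If schools do not differ in change (r = 0), the rate is 5%. At ICC 0.05 the true standard error is 1.3 to 2.1 times the modelled one.

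**Step 4: check by simulation.** With 20,000 trials per value at m = 136, the intercept-only test rejected in 13.6% at r = 0.005, 20.3% at 0.01, 30.6% at 0.02 and 48.1% at 0.05. The formula gives 13.0%, 20.1%, 30.8% and 48.1%.

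**Step 5: with the school level kept.** In the same simulations, comparing school mean changes on 8 − 2 = 6 degrees of freedom rejected in 4.7% to 5.4% for r from 0 to 0.05. In a balanced design this is what a school-by-time random effect with a small-sample correction amounts to.

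**The case against.** The strongest reply is that the faulty model is not in the article. The text says repeated measures, clustering by school and class, and small-sample correction. A school-by-time random effect, a change-score model with a school intercept, or a baseline-adjusted follow-up model would each satisfy that wording and hold about 5%. Random-effects structure is commonly left to an analysis plan or full protocol, and neither is shown. This stands: a reader might infer that the plan tests these outcomes as if pupils had been randomised, and the article does not say so. The point survives as a correctable weakness, because the article itself chose a separate approach for these outcomes, and the plainest model that fits its wording defeats the protection it sets out for eight schools.

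Two other inferences go too far. One is that every secondary outcome except intention is affected. The sentence lists knowledge, attitudes, beliefs, resistance skills and mental well-being; it does not separately name physical health, stress, anxiety or depression. The other is that the intention model is known to be sound by contrast. The Secondary outcome measures section also describes intention in terms of change in scores, and the Analysis section does not say that its outcome is the 1-month score, so that contrast is only partly documented.

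Finally, feasibility is primary, no progression criterion uses an efficacy result, and results are to be read for direction and magnitude rather than p-values. That limits the consequences. It does not remove them: a 0.05 level is still set, and cautious reading does not widen an interval that is too narrow.

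**Conclusion.** The point holds conditionally. If the repeated-measures models carry only time-constant school and class intercepts, the arm-by-time tests would have a false-positive rate of about 7% to 48% at nominal 5% over the assumed range, and 13% to 34% at a school ICC of 0.05. These figures rest on assumed ICCs, correlations over time and a pupil autocorrelation of 0.5, none of which the article gives, and on a model that it permits but does not prescribe. The rate returns to 5% if schools do not differ in their change, or to about 5% if that variation is modelled. Given the exploratory status, this is a worthwhile, cheap improvement and not a threat to the trial's main purpose.

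**What to change.** State in the Analysis section that, for the continuous outcomes in this list, the model takes the 1-month score as outcome, with the pupil's baseline score as covariate, arm, and random intercepts for school and class, fitted by REML with Kenward–Roger. There the school intercept does not cancel, and the arm effect is judged at school level.

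If a repeated-measures model is preferred, state that it includes school-by-time and class-by-time random effects, and that the arm-by-time contrast is reported with Kenward–Roger degrees of freedom of about 6. The estimated school-by-time variance could then be reported for planning the definitive trial.

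The change needs one sentence and no new data. The cost is wider intervals and fewer nominally significant results.

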Given that adolescents spend a considerable portion of their time in schools, educational settings represent a key platform for promoting adolescent health and well-being [18, 19]. Schools have the capacity to reach the vast majority of adolescents, including those who may not regularly engage with health services [20]. Global evidence demonstrates that school-based interventions can be effective in preventing tobacco initiation through various approaches such as classroom lessons, anti-tobacco messaging, and peer communication [21–23].

Bangladesh, a densely populated LMIC, ranks among the top ten countries globally for tobacco use, encompassing both combustible and non-combustible products [24, 25]. With approximately 36 million adolescents constituting 22.0% of the population in the country, the situation demands attention [26]. According to the Global School-based Student Health Survey (2014), 9.8% of school-going adolescents in Bangladesh use tobacco, with a gender disparity of 13.8% among boys and 2.0% among girls [27]. Additionally, 31.1% of adolescents are exposed to tobacco smoke at home, and 59.0% are exposed in enclosed public places [28]. Multiple factors contribute to adolescent tobacco initiation, including familial and peer influences, low socioeconomic status, impulsivity, and mental health disorders [29]. Notably, the prevalence of common mental disorders among Bangladeshi adolescents is estimated to range between 25 and 37%, highlighting the need for targeted interventions [26, 30]. However, Bangladesh faces several challenges, including the ubiquitous availability of tobacco products, weak enforcement of existing regulations, and the absence of context-specific preventive interventions [24, 25, 31]. At present, there is no intervention programme in Bangladesh specifically designed to prevent tobacco initiation among adolescents while simultaneously promoting health and well-being.

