#### Health and well-being

Health and wellbeing will be assessed using the following validated scales. To assess physical health state, students will rate their overall physical health on a 5-point scale, with higher scores indicating better health. Mental well-being will be measured using the Short Warwick–Edinburgh Mental Well-being Scale, with scores ranging from 7 to 35 [44, 45]. Perceived stress will be evaluated using the 10-item Perceived Stress Scale [46]. This widely recognised scale assesses the extent to which individuals perceive situations in their lives as stressful. Students’ anxiety will be assessed using the Generalized Anxiety Disorder-7 scale (GAD-7), a 7-item 4-point Likert scale, with scores ranging from 0 to 21 [30]. The Patient Health Questionnaire-9 scale (PHQ-9), a 9-item 4-point Likert scale, with scores ranging from 0 to 27, will be used to assess depression [47] These scales, chosen for their validity and reliability, offer a comprehensive evaluation of adolescents' mental health and well-being, encompassing positive aspects, perceived stress, anxiety, and depressive symptoms. The structured responses provided by students will contribute valuable data for understanding the effect of the IATIP on mental health outcomes.

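### The example mental-health subgroup is stated only as good versus poor, although full-range scores are collected; a baseline-score interaction would give a more precise exploratory estimate

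*Protocol article*

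**What the plan says.** The subgroup list in the Analysis section is introduced as examples and ends: "mental health condition = good vs poor, etc.) to provide preliminary estimates of potential differential effects". For mental health it names two levels and nothing else: no scale, no cut, no time point. It does not mention an interaction with a score.

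The Health and well-being section describes what is measured:
- "Mental well-being will be measured using the Short Warwick–Edinburgh Mental Well-being Scale, with scores ranging from 7 to 35"
- "Perceived stress will be evaluated using the 10-item Perceived Stress Scale"
- GAD-7, "a 7-item 4-point Likert scale, with scores ranging from 0 to 21"
- PHQ-9, "a 9-item 4-point Likert scale, with scores ranging from 0 to 27"

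The abstract gives the timing: "Data will be collected through structured questionnaires at baseline and at 1-month follow-up". Baseline scores should therefore be available.

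The Analysis section calls the subgroup work exploratory and not confirmatory, and says it should help to design a definitive trial. For the main exploratory model it plans the Kenward-Roger correction because there are only eight schools. The Progression criteria section covers recruitment, retention, fidelity and acceptability, and uses no subgroup result.

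**The concern.** Cutting a score into two groups treats a pupil just past the cut like the most distressed pupil and discards the variation within each group. The estimated difference in effect then has a wider interval than the same data could give, and its value depends on where the cut falls. The four scales run in different directions (well-being against stress, anxiety and depression), so good versus poor can be formed in several ways.

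What is at stake is modest. The Background section builds part of the rationale on the link between mental health and tobacco use, so this moderator is of real interest. The stated purpose is a preliminary estimate for planning, and for that purpose precision is what counts.

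**Working it through.** **The plan's own figures.** The plan gives no figure for this subgroup. Its one precision figure, ±2.0% for 85% retention in 1280 pupils, reproduces: 1.96 × √(0.85 × 0.15 / 1280) = 0.0196. It does not bear on the subgroup.

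**Inputs.**
- From the protocol: eight schools, about 1280 pupils, 85% retention as the example value. This gives 1280 / 8 = 160 per school, and 0.85 × 160 = 136 followed.
- Assumption: the share called poor. The plan states none. The nearest figure is in the Background: "the prevalence of common mental disorders among Bangladeshi adolescents is estimated to range between 25 and 37" per cent. That is a population prevalence of disorders, not a share above a cut on these scales, so a median split is shown as well.
- Assumption: a roughly normal score and effect modification that is linear in it.

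**Step 1: no variation in slope between schools.** Splitting a normal score so that a proportion p is poor keeps a fraction E = φ(z_p)² / [p(1 − p)] of the information on the interaction. The standard error grows by 1/√E.

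| Share poor | φ(z_p) | E | Loss | Standard error |
|---|---|---|---|---|
| 25% | 0.3178 | 0.539 | 46% | × 1.36 |
| 31% | 0.3528 | 0.582 | 42% | × 1.31 |
| 37% | 0.3776 | 0.612 | 39% | × 1.28 |
| 50% | 0.3989 | 0.637 | 36% | × 1.25 |

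A simulation with eight schools of 136, school fixed effects and an assumed interaction of 0.15 SD per SD gave losses of 47%, 39% and 38% at 25%, 37% and 50% poor.

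**Step 2: skewed scores.** With right-skewed, rounded scores bounded at 0 to 27 (gamma shapes 1 to 4, mean about 6), the loss was 32-40% when 23-40% were poor, and 40-47% near a median split.

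**Step 3: slope varying between schools.** Schools are randomised, so variation in the moderator slope between schools adds to the error of either analysis. Take residual variance 1 and slope SD τ (assumed). The variance of one school's slope is s + τ² with the full score and, on the same scale, s/E + τ² with the split, where s = 1/136 = 0.00735. At 31% poor, s/E = 0.00735 / 0.582 = 0.01264.

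| τ | Full score | Split | Loss = 1 − full/split |
|---|---|---|---|
| 0.05 | 0.00985 | 0.01514 | 35% |
| 0.10 | 0.01735 | 0.02264 | 23% |
| 0.15 | 0.02985 | 0.03514 | 15% |

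**Step 4: what this means with eight schools.** Compare four school slopes with four. The standard error is √(2v/4), where v is the variance in the table, and the test is a two-sided 5% t test on 6 degrees of freedom. For an assumed interaction of 0.17 SD per SD, power is about 53% (full score) against 38% (split) at τ = 0.05, 34% against 27% at 0.10, and 22% against 19% at 0.15. With τ = 0 it is 65% against 44%. Neither analysis is well powered.

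**The case against.** The strongest reply is that good versus poor is one illustration in an open list, in a condensed article, for an exploratory analysis in a feasibility pilot. The text promises preliminary estimates, weighs direction and size above p-values, and lets no progression criterion rest on a subgroup. All of that stands, and it keeps the point small. It does not remove the point: the two-level form is the only one stated, and the loss comes from that form whatever cut is later chosen.

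Three stronger readings are tempting, and the document does not support them.
- A reader might take a loss of 40-45% as a property of the plan. It is not: scale, cut and share are all unstated, and even the choice of baseline as the time point is an inference. The loss also shrinks when slopes vary between schools, and if the effect changes at a threshold the split need lose nothing.
- A reader might infer that mental health is the only collapsed moderator. Family socioeconomic status is also shown in two groups, low against middle or high income, and the Covariates section records place of living in several categories. Mental health differs in that multi-item scale scores are already in hand.
- A reader might infer that the full score would make the subgroup analysis adequately powered. With eight schools it would not.

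A further fair objection is that separate models for several scales would multiply exploratory estimates. Naming one score avoids this.

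**Conclusion.** The point holds as an inexpensive improvement, not as an error. Under linear effect modification and a roughly normal score, the split costs about 36-46% of the information on the differential effect: 36% at a median split, and 39-46% if 25-37% are poor. Skewed scores give 32-47%. If the moderator slope varies between schools with an assumed SD of 0.05 to 0.15, the loss is about 15-35%. The share poor, the shape of the score, linearity and the slope SD are all assumptions; the document fixes none of them. The gain is a tighter preliminary estimate that does not depend on a cut. No feasibility conclusion or progression decision changes.

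**What to change.** In the subgroup sentence of the Analysis section, replace the good-versus-poor contrast with an arm-by-baseline-score interaction in the mixed model, using one continuous score named in advance (for example PHQ-9). Add a linearity check, such as a squared term or spline. Report the interaction slope with its 95% confidence interval, using the small-sample correction already planned. Keep good versus poor, with a cut stated in advance, for display only.

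The cost is one sentence of protocol text and a few lines of Stata, with no new data. The downside is that a slope is slightly harder to explain than two groups, and linearity has to be checked.
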